### Study timeline

The first clinic visit starts with written informed consent, and when participants are eligible, the baseline assessment will be performed. The baseline assessment consists of questionnaires (frailty status, risk of sarcopenia, self-reported mobility limitations, QoL and healthcare costs) and measurements (physical function, muscle strength and body composition). See below ‘primary and secondary outcomes’ and ‘other measures’ for details on these assessments. An accelerometer will be attached to measure physical activity for 7 subsequent days.

After the baseline assessment, participants will be randomised to one of the three study groups done by the nutritionists and they will inform the participants in which group they are allocated to. Participants randomised to one of the two intervention groups will be invited for a consultation meeting at the clinic to receive their personalise d dietary advice, and personalised advice on optimising the timing of protein intake in close proximity of usual physical activity (intervention group 2 only). This will take place within 2 weeks after the baseline assessment since the personalised advice needs to be composed by the nutritionist. The baseline assessment is considered the start of the study period for participants of the control group, while the consultation meeting is considered the start of the study period for participants of the intervention groups.

One week prior to the 3-month follow-up visit, dietary intake will be assessed again by means of a combination of three food diaries and three 24-hour dietary recalls. The 3-month follow-up visit will take place at the clinic and includes measurement of BW, assessment of self-reported mobility limitations, risk of sarcopenia, QoL, healthcare costs and the accelerometer will be attached to measure physical activity for 7 subsequent days.

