Self-reported mobility limitations will be assessed by means of a questionnaire; ‘Because of your health, how much difficulty do you have walking 400 metre?’ and ‘Because of your health, how much difficulty do you have climbing 10 steps?’ Participants will respond using a 5-level Likert scale: ‘no difficulty’, ‘a little difficulty’, ‘some difficulty’, ‘a lot of difficulty’ and ‘unable to do the activity’. Mobility limitation is defined as two consecutive reports of having any difficulty walking 400 m or climbing 10 steps without resting due to a health or a physical problem.

QoL will be measured using the EuroQol 5D-5 L Questionnaire.^63^

Incident frailty will be assessed using the Fried criteria.^64^ Participants will be considered ‘frail’ when three or more components are present. Those with no components will be considered ’robust’, whereas those with one or two components will be considered ’prefrail’. The criteria include (1) self-reported unintentional weight loss (>4 kg in past 6 months), (2) self-reported exhaustion (based on two questions from the Center for Epidemiologic Studies Depression Scale on exhaustion in the past week at baseline and follow-up: ‘I felt that everything I did was an effort’ and ‘I could not get going’. Scores range from 1 ‘rarely or none of the time’ to 4 ‘always or most of the time’. A score of 3 or 4 on either question indicates exhaustion,^65^ (3) weakness (grip strength in the lowest 20% of the whole study population based on the mean of the maximum scores, adjusted for gender and BMI), (4) slow walking speed (walk time on the 4 m walk test in the slowest 20% of the whole study population, adjusted for gender and height), and (5) low physical activity (total counts per week based on the accelerometer data in the lowest 20% of physical activity for each gender). Incident frailty is considered deterioration of frailty status; that is, from robust at baseline to prefrail or frail at follow-up or from prefrail at baseline to frail at follow. Frail participants at baseline will be excluded from these analyses.

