Incidence of sarcopenia risk will be assessed with the SARC-F Questionnaire^66^; how much effort do you experience when (1) lifting and carrying a bag of 4.5 kilo, (2) walking across a room, (3) transferring from a chair or bed, (4) climbing a flight of 10 stairs and (5) how many times have you fallen in the past year. Answering option include no effort (0 points), a bit of effort (1 point) and a lot of effort (2 points), where a score equal to or greater than 4 is predictive of sarcopenia and poor outcomes. Participants with risk of sarcopenia at baseline will be excluded from these analyses.

Incidence of malnutrition will be defined as BMI <22.0 kg/m^2^ or unintentional weight loss >5% in the last 6 months. Malnourished participants at baseline will be excluded from these analyses.

A modified version of the Resource Utilisation in Dementia Questionnaire^67^ will be used to collect data on healthcare and social utilisation costs over the period 3 months prior to baseline, 3 months prior to the 3-month follow-up visit and 3 months prior to 6-month follow-up visit. Costs include costs of primary and secondary care, complementary care, informal care and home care.

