#### Statistical analyses plan

Statistical reporting will be according to the Consolidated Standards of Reporting Trials standards.^70^ The collected data at the two study sites will be pooled together at the Amsterdam site, with a variable indicating study site. All statistical analyses on primary and secondary outcome measures will be performed by an independent statistician blinded for group allocation. Baseline characteristics will be described (percentages, means±SDs) by study group.

The primary analyses will be based on the intention-to-treat principle, that is, data from participants allocated to the intervention groups will be analysed as part of those groups, irrespectively of their level of adherence to the advice. Multiple imputation using Multivariate Imputation by Chained Equations will be used to impute missing cost and effect data. The continuous primary outcome (change in 400 m walk time) will be analysed using mixed model regression analyses with study site as random variable. We will adjust for baseline 400 m walk time as well as baseline protein intake (g/kg aBW/day) and sex (the stratification factors for randomisation). We will compare intervention effects of the respective intervention groups versus the control group. Effects will also be expressed in Cohen’s d and the corresponding 95% CIs will be calculated, which allows comparison between intervention effect estimates between different outcome measures. The secondary outcomes and other measures will be analysed using mixed model regression analogously to the primary outcome. For binary secondary outcomes, generalised estimating equation models will be used. With regard to time-to-event analyses (incident sarcopenia risk and mobility limitations) Cox proportional hazard models will be used. Time-to-event is defined as the time of the start of the study period to the date of the first occurrence of the event (3-month follow-up visit or 6-month follow-up visit). Participants who do not meet these criteria will be censored at the latest time we had information available. We will perform subgroup analyses stratified by baseline protein intake (<0.9 or 0.9–1.0 g/kg aBW/day), sex and baseline 400 m time (based on median) for the primary and secondary outcomes.

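### Mobility limitation (secondary outcome): the two-report definition, the three reporting occasions and the 3- or 6-month Cox event times do not fit together, so the hazard ratio mixes persistence with onset and omits difficulty first reported at 6 months

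*Protocol article*

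**What the plan says.** **Definition (Secondary outcomes).** The rule reads "Mobility limitation is defined as two consecutive reports of having any difficulty walking", and difficulty on the stair item counts equally. There are two items, one on walking 400 m and one on climbing ten steps: "Participants will respond using a 5-level Likert scale". Because any difficulty qualifies, every answer other than the lowest category is a positive report.

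**Occasions (Study timeline, Table 1).** At baseline: "The baseline assessment consists of questionnaires (frailty status, risk of sarcopenia, self-reported mobility limitations, QoL and healthcare costs". The 3-month visit "includes measurement of BW, assessment of self-reported mobility limitations, risk of sarcopenia, QoL, healthcare costs". The 6-month visit repeats the baseline measurements and is the final one. Randomisation follows the baseline assessment.

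**Analysis (Statistical analyses plan).** The model is fixed by this sentence: "With regard to time-to-event analyses (incident sarcopenia risk and mobility limitations) Cox proportional hazard models will be used". For the event date, the same section states: "Time-to-event is defined as the time of the start of the study period to the date of the first occurrence of the event", and it names the 3-month and 6-month visits as the two possible dates. Participants without an event are censored at the last available information.

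**Baseline cases.** For sarcopenia risk, "Participants with risk of sarcopenia at baseline will be excluded from these analyses". Equivalent sentences are given for frailty and malnutrition. None is given for mobility limitation.

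**The concern.** A rule that needs two consecutive reports needs a visit after the first report to confirm it. With three occasions, the last has no successor and the first lies before randomisation. Onset first seen at the last visit cannot be confirmed, and a pair completed at 3 months must use the pre-randomisation report.

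The trial asks whether dietary advice preserves function over 6 months, so a reader of a Cox hazard ratio for mobility limitation will take it as the effect on developing a limitation. If many of the counted events are old difficulty that persisted, and onset in the second half of follow-up is left out, the number answers a different question. The events that would be most informative are also partly thrown away.

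Eligibility does not remove the problem. Participants must complete 400 m within 15 minutes, but someone who can do so may still report a little difficulty with walking or stairs.

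**Working it through.** The plan states no figure for this outcome, so there is none to reproduce. The check is an enumeration of the stated rules.

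**Step 1: all response patterns.** Write 1 for any difficulty and 0 for none, in the order baseline, 3 months, 6 months. There are 2 × 2 × 2 = 8 patterns.

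| Pattern | Event if dated at the second report | Event if dated at the first of the two reports | First report, baseline difficulty excluded |
|---|---|---|---|
| 0-0-0 | none | none | none |
| 0-0-1 | none | none | 6 months |
| 0-1-0 | none | none | 3 months |
| 0-1-1 | 6 months | 3 months | 3 months |
| 1-0-0 | none | none | excluded |
| 1-0-1 | none | none | excluded |
| 1-1-0 | 3 months | baseline | excluded |
| 1-1-1 | 3 months | baseline | excluded |

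**Step 2: dating when the definition is first met.** Both patterns that give a 3-month event (1-1-0, 1-1-1) carry difficulty at baseline. The only event in someone free of difficulty at baseline is 0-1-1, dated at 6 months. Pattern 0-0-1 is never an event.

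**Step 3: can another reading rescue the rule?**
- *Date at the first of the two reports.* 0-1-1 moves to 3 months, 1-1-0 and 1-1-1 fall at baseline (at or before time zero), and no 6-month event is possible. That contradicts the two event times in the Statistical analyses plan.
- *Exclude baseline difficulty but keep the two-report rule.* Only 0-1-1 remains, so there is one event time and no 3-month events when dated at the second report.
- *Read the outcome as change, as the list of secondary outcomes does.* Unchanged difficulty (1-1-1) is an event while a deterioration (0-0-1) is not.

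On all three, 0-0-1 is lost.

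**Step 4: size, under assumed values.** The document gives neither the prevalence nor the onset rate of difficulty, so these are illustrations with complete data.

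(a) Share of new onsets first seen at 6 months. Let h be the risk of a first report in each 3-month interval, equal in both, among those free at baseline. Then the share is (1 − h)h / [h + (1 − h)h] = (1 − h)/(2 − h).
- h = 5%: 0.95/1.95 = 0.49.
- h = 10%: 0.90/1.90 = 0.47.

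For one group of 88 with 20% reporting difficulty at baseline and h = 10%, 88 × 0.80 = 70.4 are free at baseline. New at 3 months: 7.04. New at 6 months: 70.4 × 0.90 × 0.10 = 6.34. Lost: 6.34 of 13.38, or 47%.

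(b) Share of counted events with difficulty at baseline, dating at the second report. Let b be baseline prevalence and s the chance that difficulty is repeated at the next visit, the same for old and new difficulty. The share is bs / [bs + (1 − b)hs] = b / [b + (1 − b)h]; s cancels.
- b = 10%, h = 10%: 0.10/(0.10 + 0.09) = 0.53.
- b = 30%, h = 5%: 0.30/(0.30 + 0.035) = 0.90.

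**The case against.** Several objections deserve weight.

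**One baseline report is not the outcome.** Under the protocol's definition, a participant with 1-1 first becomes a case at 3 months. This stands as a limit on wording: the 3-month events are people with difficulty already reported, not people who already met the definition. The statement also depends on dating at the second report. That is the natural reading, and the only one of the two that allows events at both visits, but the text does not spell it out.

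**Incidence may not be intended.** The objectives and the list of secondary outcomes use incidence for frailty, sarcopenia risk and malnutrition, and place mobility limitations among the changes. In the Cox sentence, it is unclear whether the word incident covers both outcomes. A confirmed limitation that includes persistence may be what was wanted, which would explain the absent exclusion. This leaves the aim open, but a first-occurrence Cox model with 3- and 6-month events fits that aim poorly, and 0-0-1 is still lost.

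**The two-report rule has a purpose.** It screens out transient difficulty, which matters for self-report in an unblinded trial. That stands. Pattern 0-1-0 should therefore not be held against the rule, and the size in (a) counts only what the visit schedule loses.

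**Stronger readings that the document does not support:**
- A reader might infer that anyone missing a follow-up visit is simply censored. The plan also imputes missing effect data by chained equations and does not say how this combines with the censoring rule.
- A reader might infer that 6-month events are impossible. They are not, since 0-1-1 is one when dated at the second report.
- A reader might extend the defect to sarcopenia risk. That outcome excludes baseline cases, needs one assessment at or above its threshold, and can have events at both visits.

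**Conclusion.** The point holds as a mismatch between rules that the article itself states: definition, occasions and event times. It is not a detail left to a separate analysis plan. That 0-0-1 never counts follows from the enumeration on any reading. That all 3-month events have pre-randomisation difficulty follows once the event is dated when the definition is first met.

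The resulting hazard ratio mixes persistence with onset and omits onset after month 3. Under the assumed equal onset risk of 5–10% per interval, 47–49% of new onsets are lost to the schedule. Under the assumed baseline prevalence of 10–30%, 53–90% of counted events are in people with baseline difficulty. Only the direction of these figures should be relied on.

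It would be tempting to conclude that the treatment comparison is biased. The document does not support that: the baseline report precedes randomisation, so baseline difficulty is balanced across arms in expectation. The harm is to interpretation and to the number of informative events. One secondary outcome is affected; the primary outcome and the sample size are not. It should be fixed, but it does not threaten the trial's main conclusion.

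**What to change.** Amend the mobility-limitation text before the analysis is run:

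1. Exclude from this analysis participants who report any difficulty on either item at baseline, in line with the other three outcomes.
2. Define the event as the first report of any difficulty at 3 or 6 months. Patterns 0-1-0 and 0-1-1 are then events at 3 months and 0-0-1 at 6 months.
3. Analyse it with a model suited to two event times and the planned covariates, for example a discrete-time complementary log-log model, or a Cox model with suitable handling of ties.
4. Report the confirmed pattern 0-1-1 as a supportive binary outcome at 6 months.

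No new data are needed. The change does alter the definition of a secondary outcome, so it should be recorded as such. Two costs remain. A single self-report in an unblinded trial is noisier than a confirmed one, which the supportive outcome partly covers. Participants with baseline difficulty also leave this analysis, so its sample is smaller.

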#### Other measures

BW will be measured without shoes in underwear to the nearest 0.1 kg using a digital calibrated scale (Finland; SECA 877, the Netherlands; Marsden M-520). Body height will be measured to the nearest millimetre using a SECA stadiometer for mobile height measurements (Finland; SECA 217, the Netherlands; SECA 214). Corrections will be made to adjust the measured BW for clothing, shoes or a cast (minus 1 kg for each element), and to adjust the measured body height for shoes (minus 1 cm). Change in BW and BMI at 3 months and 6 months will be calculated. As the personalised dietary advice is isocaloric, no significant difference in BW or BMI is expected. Physical activity will be objectively assessed by means of an accelerometer (Axivity, AX3) during 7 subsequent days after each clinic visit (baseline, 3-month follow-up visit and 6-month follow-up visit). The accelerometer will be attached by a nutritionist to the frontal part of the right thigh in the midpoint between iliac crest and patella bone when sitting down, with a surgical plaster. Participants can perform any physical activity as the accelerometer is water resistant. Appetite will be measured with Simplified Nutritional Appetite Questionnaire.^68^ Dietary intake will be assessed by means of a combination of three food diaries and three 24-hour dietary recalls prior to the 3-month follow-up visit and the 6-month follow-up visit.

### Sample size and statistical analyses

#### Sample size

The study is powered to detect a substantial meaningful change of 28 s (SD=61 s)^69^ between the respective intervention groups and the control group on the primary outcome walk time on the 400 m walk test, assuming a two-sided test at α=0.05 with a power of 0.8. For this, 75 participants per group are needed, which is 225 in total. Assuming a drop-out of 15% (which was reported in a comparable study of Bhasin *et al*,^19^ the total number of study participants to be included in the study is n=264. Therefore, we aim to include a total of n=132 at each study site (n=44 per study group per study site).

#### Statistical analyses plan

Statistical reporting will be according to the Consolidated Standards of Reporting Trials standards.^70^ The collected data at the two study sites will be pooled together at the Amsterdam site, with a variable indicating study site. All statistical analyses on primary and secondary outcome measures will be performed by an independent statistician blinded for group allocation. Baseline characteristics will be described (percentages, means±SDs) by study group.

The primary analyses will be based on the intention-to-treat principle, that is, data from participants allocated to the intervention groups will be analysed as part of those groups, irrespectively of their level of adherence to the advice. Multiple imputation using Multivariate Imputation by Chained Equations will be used to impute missing cost and effect data. The continuous primary outcome (change in 400 m walk time) will be analysed using mixed model regression analyses with study site as random variable. We will adjust for baseline 400 m walk time as well as baseline protein intake (g/kg aBW/day) and sex (the stratification factors for randomisation). We will compare intervention effects of the respective intervention groups versus the control group. Effects will also be expressed in Cohen’s d and the corresponding 95% CIs will be calculated, which allows comparison between intervention effect estimates between different outcome measures. The secondary outcomes and other measures will be analysed using mixed model regression analogously to the primary outcome. For binary secondary outcomes, generalised estimating equation models will be used. With regard to time-to-event analyses (incident sarcopenia risk and mobility limitations) Cox proportional hazard models will be used. Time-to-event is defined as the time of the start of the study period to the date of the first occurrence of the event (3-month follow-up visit or 6-month follow-up visit). Participants who do not meet these criteria will be censored at the latest time we had information available. We will perform subgroup analyses stratified by baseline protein intake (<0.9 or 0.9–1.0 g/kg aBW/day), sex and baseline 400 m time (based on median) for the primary and secondary outcomes.

Per-protocol analyses will also be conducted as a sensitivity analysis. Effect estimates for change in primary and secondary outcome measures will be calculated for participants from the intervention groups who reached the protein target of at least 1.2 g/kg aBW/day after both 3 and after 6 months (mean protein intake based on the three 24-hour dietary recalls) versus participants from the control group. Data will be analysed using SPSS (IBM SPSS Statistics, Version 26). A two-sided p value of 0.05 is considered statistically significant.

The cost-effectiveness analysis will be performed from a healthcare perspective. Total mean costs during the study will be related to physical functioning (the 400 m walk test) and change in quality-adjusted life-years based on the EuroQol 5D Questionnaire. Mixed model regression analyses will be used to estimate differences in the primary outcome of the respective intervention groups versus the control group. Linear regression analyses will be used to estimate differences in QoL (expressed as quality-adjusted life-years) and healthcare costs. Incremental cost-effectiveness ratios will be calculated by dividing the difference in costs by the difference in effects. Statistical uncertainty will be estimated using bias-corrected accelerated bootstrapping (5000 replications) and will be presented using cost-effectiveness planes and cost-effectiveness acceptability curves.

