**Trial registration number:**

ClinicalTrials.gov Registry (NCT03712306).

Strengths and limitations of this studyThis large randomised controlled trial addresses a key question whether dietary advice to increase protein intake to ≥1.2 g/kg adjusted body weight (aBW)/day is beneficial for physical functioning in community-dwelling older adults.This trial will also examine the additional effect of the timing of protein intake in close proximity of usual physical activity on change in physical functioning.Participants included had a habitual protein intake of <1.0 g/kg aBW/day.The lack of blinding of the study participants and nutritionists who also collect data on all outcome measures is a limitation of the study design.Another limitation of this study is that the biological value of the total protein intake (ie, type of amino acids) is unknown.

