## Discussion

There is an ongoing discussion whether the EFSA RDA of 0.8 g protein/kg BW/day is sufficient for older adults and whether it should be increased to at least 1.0–1.2 g protein/kg BW/day to support muscle health and functioning. National guidelines of some European countries already increased their RDA, that is, the RDA of the German-speaking countries (D-A-CH) is increased to 1.0 g/kg BW/day,^86^ and the Nordic Nutrition Recommendation has increased their RDA to 1.2 g/kg BW/day.^87^ The PROMISS trial is the first RCT which will investigate the effect of personalised dietary advice aiming at increasing protein intake and the combined effect of personalised dietary advice aiming at increasing protein and the timing of protein intake in close proximity of usual physical activity, on change in physical functioning after 6 months among community-dwelling older adults (≥65 years) with a habitual protein intake of <1.0 g/kg aBW/day. The PROMISS trial will therefore provide additional insight to the question whether the current EFSA RDA for protein for older adults should be increased to 1.2 g/kg aBW/day, and whether optimal timing of protein intake will additionally benefit physical functioning.

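### The article promises evidence on whether timing of protein intake adds benefit, but every planned comparison is with control, so the contrast that estimates this (group 2 minus group 1) is not specified

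*Protocol article*

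**What the plan says.** **The promise.** The strengths and limitations box (printed under the trial registration number) says: "This trial will also examine the additional effect of the timing of protein intake". The Discussion says the trial will give insight into "whether optimal timing of protein intake will additionally benefit physical functioning". The abstract's discussion paragraph makes a similar promise.

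**The objective.** The Introduction is narrower. It makes the effect of the protein advice the primary objective and then adds the combined effect of protein advice plus timing advice.

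**The planned comparisons.** All are with control:
- Sample size: the effect to be detected is "between the respective intervention groups and the control group on the primary outcome walk time".
- Primary analysis: "We will compare intervention effects of the respective intervention groups versus the control group". Secondary outcomes follow the same pattern.
- Per-protocol analysis: intervention participants who reached the protein target, against control.
- Cost-effectiveness analysis: each intervention group against control.

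**The significance level.** The sample size is set "assuming a two-sided test at α=0.05 with a power of 0.8", and the analysis section adds: "A two-sided p value of 0.05 is considered statistically significant".

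**The concern.** According to the Intervention section, group 2 gets group 1's dietary advice plus the advice on timing. What timing adds is therefore the difference between groups 2 and 1, and no section plans, sizes or mentions that difference. The Introduction's combined effect is a different quantity: group 2 minus control mixes the effect of more protein with the effect of timing.

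If the direct contrast is not fixed in advance, the only material the plan supplies for a statement about timing is two results against the same control. One being significant and the other not is weak evidence that the two groups differ. A reader also needs to know beforehand how precise a timing estimate this trial can give, because a non-significant difference could easily be misread as showing that timing does not matter.

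**Working it through.** **Inputs.** From Sample size: difference 28 s, SD 61 s, two-sided α 0.05, power 0.80, 75 evaluable per group, 15% drop-out, 264 in total. From Randomisation: 1:1:1 allocation. Assumed here because the article gives no figure: a common benefit of 20 s as an alternative to 28 s, and a timing effect of 14 s.

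**1. The plan's own figure.** n per group = 2 × [61 × (1.960 + 0.842) / 28]² = 74.5, rounded up to 75. Then 3 × 75 = 225, and 225 / 0.85 = 264.7, against 264 stated. The figure reproduces. It applies to one two-group comparison at an unadjusted 0.05.

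**2. Standard error of any two-group contrast.** SE = 61 × √(2/75) = 9.96 s.

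**3. What side-by-side reading would do if timing adds nothing.** The two control contrasts share the control group, so with equal groups their correlation is 0.5. Treat the two test statistics as bivariate normal, each with mean (benefit / SE).

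| Common true benefit | Each contrast significant | Both significant | Exactly one significant | Group 2 only |
|---|---|---|---|---|
| 28 s (mean 2.81) | 0.803 | 0.691 | 2 × (0.803 − 0.691) = 0.224 | 0.112 |
| 20 s (assumed; mean 2.01) | 0.519 | 0.353 | 2 × (0.519 − 0.353) = 0.333 | 0.166 |

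By symmetry, half of the discordant trials would appear to favour timing and half would appear to count against it.

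**4. What the direct contrast can deliver.** For group 2 minus group 1 with 75 per group:
- 95% CI half-width = 1.96 × 9.96 = 19.5 s.
- Difference detectable with 80% power = 2.80 × 9.96 = 27.9 s, which is the whole effect assumed against control.
- Power for an assumed 14 s timing effect = Φ(14/9.96 − 1.96) = Φ(−0.55) = 0.29. About 299 per group would be needed for 80%.

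**5. Side note on the two control contrasts.** If neither group differs from control, the chance that at least one contrast is significant at 0.05 (correlation 0.5) is 0.091.

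**The case against.** The best defence is that the objective as the Introduction words it is the combined effect, and group 2 against control estimates exactly that. Other parts of the Discussion also speak of a combined effect or combined benefit. This stands: the stated objectives do have planned analyses. The defect is a mismatch between the objectives and the wider promises in the abstract, the strengths box and the Discussion, and rewording those promises would also cure it.

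Three stronger readings are tempting, and the document does not support them.

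- *The timing question cannot be answered.* The three groups are randomised concurrently, so the data will allow the estimate. What is missing is the planned contrast.
- *A false claim about timing is likely.* Only 11% of trials (17% at the assumed 20 s) would show group 2 alone as significant when timing adds nothing. Even then, an error needs authors to infer timing from differing significance, and nothing in the article says they will.
- *The trial breaches its own error rate because the family-wise rate is 9.1%.* The article states a per-test level and claims no family-wise level. Whether separate arms sharing a control need adjustment is disputed, and a testing hierarchy may stand in an analysis plan that is not shown. A fixed order would also make the group 2 contrast depend on group 1's result, although the sample size powers both equally. This is a trade-off and no reason to require a change.

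On precision, the primary model adjusts for baseline walk time, and the article does not say whether 61 s is the SD of walk time or of its change. The interval may be narrower than 19.5 s, by an amount the article does not let one calculate.

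**Conclusion.** The point holds as an inconsistency between promise and analysis. Three places in the article promise evidence on what timing adds, and every comparison in the sample size and analysis sections is with control. Those comparisons serve the combined-effect objective only.

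Substituting a side-by-side reading would give discordant significance in about 22% of trials at a common 28 s benefit, with group 2 alone significant in 11%. The direct contrast would be imprecise: half-width about 19.5 s, 80% power only near 28 s, and about 29% for an assumed 14 s.

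These figures rest on 75 evaluable per group, SD 61 s in every group, normal approximations and no gain from baseline adjustment. The sample size arithmetic for the control contrasts is sound. The use of 0.05 for each control contrast merits at most a note.

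**What to change.** In the Statistical analyses plan section, add the group 2 minus group 1 contrast from the same adjusted mixed model. Report it with its 95% CI, and state that it is the only basis for any statement on the additional effect of timing. Add a sentence saying that the trial was not sized for this contrast and that modest timing effects could be missed, giving the figures above.

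Alternatively, limit the abstract, the strengths box and the Discussion to the combined effect of protein and timing advice.

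Optionally, note that the two control contrasts are each tested at 0.05 (family-wise error about 9.1%) and that the Introduction names the protein-advice objective as primary. No fixed testing order is needed.

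The first option costs one contrast from a model already planned and a few sentences. The second costs rewording only. Neither changes the sample size or trial conduct. The choice should be fixed before results by group are seen.
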